### Qualitative study

Qualitative researchers will interview healthcare professionals about their recruitment experiences, perceptions of why patients decline or consent to participation, and reasons for not approaching eligible patients. Patients and caregivers will be interviewed at two time points—following randomisation and 12 weeks later. Postrandomisation interviews will explore reasons for taking part or declining participation, views about trial recruitment approaches, hopes and expectations regarding trial participation, and any anticipated difficulties or concerns adhering to treatment allocation. Follow-up interviews will explore treatment adherence, benefits or burdens of the allocated treatment and perceptions of the impact on QoL and recovery. All interviews will use topic guides to help ensure the discussion remains relevant to addressing the study aims, while offering participants flexibility to raise issues they consider important, including those unforeseen at the study outset.

### Sample size

The recruitment target is 887 participants from around 25 UK sites over 2 years. An unadjusted sample size was calculated based on 90% power and a 5% significance level, using a two-sided two-sample t-test, for an effect size of 1/6 (0.05 minimum clinically important difference/0.3 SD) on the EQ-5D-5L at 12 weeks. This results in a sample size of 1514, increasing to 1893 assuming 20% missing data. This sample size can be reduced by accounting for correlation between baseline covariates (age, CFS) and 12 week EQ-5D-5L. It is anticipated that this correlation will be around 0.5, allowing a 25% reduction in sample size. Higher correlation will allow a larger reduction.^30^ Further, the postrandomisation measures of EQ-5D-5L at 2, 6 and 12 weeks, are assumed to have a serial correlation of 0.44 which allows a further 37.5% reduction in sample size.^30 31^ Including these reductions leads to the final target sample size of 887, with 1:1 allocation.

To check these assumptions, a sample size re-estimation will be modelled using a simulation approach based on 12 week outcome data from the first 300 participants.^30^ Due to the conservative assumptions made, particularly the assumed SD, the probability of increasing the sample size is small, and there is a larger probability it can be reduced.

Based on audits in two UK neurosurgical units, and assuming a 50% recruitment rate with staggered site opening, the target recruitment rate is 1.6 patients per site per month. An internal pilot will assess recruitment feasibility, targeting 132 patients (15% total) across 18 centres in 9 months. Progression criteria for the pilot are shown in table 2.

**Table 2 T2:** Study progression criteria

	Category		
	Red	Amber	Green
Total no recruited	≤108	109–131	≥132
Recruitment threshold (%)	≤82	83–99	100
Recruitment rate (patients per site per month)	1.07	1.33	1.63
No of sites open	<5	5–10	>10
Adherence failure	>20%	11%–20%	≤10%

Study progression criteria for the internal pilot to assess recruitment feasibility after the first 9 months of recruitment. The traffic light categories will lead to the following actions. Green: continue unchanged. Amber: make changes, including adding more sites or increasing the time period for recruitment. Red: continue stopping as study may not feasible, unless identifiable and rectifiable causes are identified. Adherence failure includes study withdrawals and cross-over (removing a collar in the collar arm, or wearing a collar in the no collar arm).

The qualitative study will recruit approximately 20 healthcare professionals and 30 patients or carers from a cross section of sites. Purposive sampling will be used to ensure representation of different ages, socioeconomic backgrounds, cognitions and residential setting among patients. Sampling decisions may be revised in light of emerging findings.

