### Outcome measures

The primary outcome measure is the EQ-5D-5L at 12 weeks postrandomisation.

Secondary outcome measures are:

Two and 6 weeks: EQ-5D-5L, Neck Disability Index (NDI), Neck Numeric Pain Scale.Twekve weeks: NDI, Neck Numeric Pain Scale, adverse events (AEs), compliance with hard collar use, analgesia use, length of hospital stay, discharge destination, bony fusion/stability on imaging, loss of muscle bulk in upper limbs using grip strength and bioimpedence.Six and 12 months: EQ-5D-5L, NDI, Neck Numeric Pain Scale, injury-related complications, mortality, health and social care visits/use, hospital admission or outpatient visits, health economics analysis.

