### Data analysis plan

The primary data analysis will be by intention to treat. A 5% two-sided significance level will be used throughout. A detailed statistical analysis plan will be developed by the study statisticians and finalised prior to locking of the trial database.

Analysis of the primary outcome will be a repeated measures analysis of covariance, including terms for treatment arm and the EQ-5D-5L responses at 2, 6 and 12 weeks. Adjustments will be made for the variables included in the randomisation minimisation algorithm. Adjustment for study site will be included as a random effect, if appropriate. The repeated measures approach enables estimation of an intervention effect at week 12 postrandomisation (primary outcome), and an overall assessment of the effect of the intervention over the 12-week period.

The 12-week NDI and Visual Analogue Scale will be analysed in a similar manner to the EQ-5D-5L. It is anticipated that results will underpin any between group differences seen in EQ-5D-5L, confirming and strengthening the clinical interpretation of the findings. All other secondary outcomes will be analysed with statistical models appropriate to the distribution of the outcome (see table 3). Where there are data recorded on multiple occasions postrandomisation, we may use an appropriate repeated measures model. Exploratory subgroup analyses by fracture type (I, II and III),^24^ CFS (<5 vs ≥5)^23^ and age (<75 vs ≥75 years) will be performed. The influence of any missing data on the robustness of the findings will be examined, for example, using multiple imputation models under a missing at random assumption. Screening logs will be analysed to assess generalisability of results.

**Table 3 T3:** Possible methods of analysis

Variable	Hypothesis	Outcome measures	Analysis methods
Baseline data	No difference between groups	Gender, age, comorbidities, injury data, radiological findings, inpatient management, CFS	Categorical variables: absolute numbers and percentages. Continuous variables: mean, median, SD, IQR.
Primary outcome			
Health-related quality of life at 12 weeks	Clinically important difference between two groups with early collar removal superior	EQ-5D-5L (continuous)	Repeated measures analysis of covariance at 2, 6 and 12 weeks, adjusting for minimisation variables
Secondary outcomes			
Pain	No difference between groups	NPRS (ordinal)	Ordinal regression

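### The 37.5% sample-size reduction matches an effect averaged over weeks 2, 6 and 12; for a separately estimated week-12 effect, the declared primary, 887 participants give about 73–75% power, not 90%

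*Protocol article*

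**What the plan says.** The Outcome measures section fixes a single time point: "The primary outcome measure is the EQ-5D-5L at 12 weeks postrandomisation". The abstract, the primary aim and Table 3 agree.

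The Sample size section starts from the same time point. Its error rates and test are "90% power and a 5% significance level, using a two-sided two-sample t-test". The difference to be detected is expressed there as an "effect size of 1/6 (0.05 minimum clinically important difference/0.3 SD) on the EQ-5D-5L at 12 weeks". This gives a "sample size of 1514, increasing to 1893 assuming 20% missing data". Two reductions follow:

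- For baseline covariates (age and frailty score): "It is anticipated that this correlation will be around 0.5, allowing a 25% reduction in sample size".
- For the repeated post-randomisation scores: a "serial correlation of 0.44 which allows a further 37.5% reduction in sample size".

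The result is 887 participants, allocated 1:1. A simulation-based re-estimation on the first 300 participants is planned. The section expects that "the probability of increasing the sample size is small, and there is a larger probability it can be reduced", citing conservative assumptions and the SD in particular.

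The Data analysis plan describes the primary analysis as a repeated measures analysis of covariance, "including terms for treatment arm and the EQ-5D-5L responses at 2, 6 and 12 weeks". It says that this approach yields an intervention effect at week 12, which it labels the primary outcome, and also an overall assessment of the effect across the 12 weeks.

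**The concern.** The two effects that the Data analysis plan distinguishes have different variances. Averaging three correlated scores reduces the variance of the averaged effect. It does not reduce the variance of the effect at the last visit. The calculation starts from a week-12 difference and ends with a saving of the size that belongs to the average. If so, the stated 90% power does not apply to the declared primary outcome. The chance of missing a true week-12 difference of 0.05, which the plan treats as the minimum clinically important difference, would then be about 25–27% rather than 10%.

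**Working it through.** **Inputs, all from the Sample size section:** difference 0.05; SD 0.30; two-sided 5%; 90% power; 20% missing; covariate correlation 0.5; serial correlation 0.44; N = 887, 1:1.

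**1. Reproduce the plan's figures.**
- Per arm: 2 × (1.960 + 1.282)² × (0.30/0.05)² = 756.5, so 757 per arm and 1514 in total.
- Missing data: 1514/0.8 = 1892.5, rounded up to 1893.
- Covariates: 1 − 0.5² = 0.75.
- Repeated measures: 1 − 0.375 = 0.625.
- 1893 × 0.75 × 0.625 = 887.3. The stated 887 is reproduced.

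**2. Identify the 37.5%.** The article gives no formula, so candidates have to be tried.
- Mean of three equally correlated scores: variance factor (1 + 2ρ)/3. At ρ = 0.44 this is 0.627, a 37.3% reduction. Exactly 37.5% corresponds to ρ = 0.4375, which rounds to 0.44.
- Adjustment for one correlated score: 1 − 0.44² = 0.806, a 19% reduction. This does not match.

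The averaging formula fits.

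**3. Power for the averaged effect.** SD 0.30 × √(0.75 × 0.625) = 0.205; 887 × 0.8/2 = 354.8 per arm; SE = 0.205 × √(2/354.8) = 0.0154; 0.05/0.0154 = 3.24; power = Φ(3.24 − 1.96) = 90.0%. The plan's claim is correct for this effect.

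**4. Power for the week-12 effect, estimated separately, week-12 completers only.** SD 0.30 × √0.75 = 0.260; SE = 0.260 × √(2/354.8) = 0.0195; 0.05/0.0195 = 2.56; power = Φ(2.56 − 1.96) = 72.7% (72.6% with the t distribution).

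**5. Most that weeks 2 and 6 can recover.** Suppose everyone missing at week 12 supplied both earlier scores.
- Share of week-12 variance explained by those scores: R² = 2 × 0.44²/(1 + 0.44) = 0.269.
- Effective fraction: 1/[(1 − 0.269)/0.8 + 0.269] = 0.845, so the effective n is 887 × 0.845 = 750.
- SE = 0.260 × √(4/750) = 0.0190; power = 75.0%.
- With independent 20% missingness at each visit instead, power is 74.7%.

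**6. What 90% power at week 12 would take (completers basis).**
- Detectable difference at N = 887: 3.242 × 0.0195 = 0.063.
- N for 0.05: 1893 × 0.75 = 1419.75, about 1420.
- SD at which 887 suffices: 0.30 × 2.563/3.242 = 0.237.

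Under the full recovery of step 5 these ease only slightly. The detectable difference is 3.242 × 0.0190 = 0.062, and N is 1514 × 0.75/0.845 = about 1344.

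**7. Sensitivity.**
- No missing data at all: power is 81.7%.
- If 0.44 is a raw correlation and covariates correlate 0.5 with every visit (an assumption), the residual correlation is (0.44 − 0.25)/0.75 = 0.25. Week-12 power is then 72.7–73.6%.

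**The case against.** **Constant effect.** The strongest defence is a model with one treatment effect common to all visits. The collar arm is treated throughout the 12 weeks, so a constant effect is a possible working assumption. Under it the common effect is also the week-12 effect, and 887 gives about 90% power. This works only if the effect is 0.05 at every visit, which the article does not state. The Data analysis plan also treats the week-12 and overall effects as two different things. For illustration, if the effect grew as 0, 0.025 and 0.05, the average would be 0.025 and power for the averaged effect about 37%.

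**Origin of the 37.5%.** The formula is inferred, and the sources cited for it are not at hand. The match is close and the obvious alternative fails, so the inference is strong. Whatever the origin, the power in steps 4 and 5 of the working follows from the stated inputs.

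**Conservative SD.** The plan says that its SD is conservative, and an SD of about 0.237 or less would restore 90% at week 12. The article gives no lower SD, and hoping that one input is too large does not make the calculation right on its own inputs.

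A reader might also infer three stronger points, which the document does not support:

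- *The primary model wrongly omits an arm-by-visit term.* The Data analysis plan promises a week-12 effect, which implies visit-specific estimation. The full specification is left to the statistical analysis plan.
- *The serial correlation of 0.44 is not conservative.* Nothing in the article suggests that it is too low, and the residual value after adjustment could be lower.
- *The re-estimation will repeat the error, so the expectation that an increase is unlikely should be withdrawn.* The article says that the re-estimation checks the assumptions using 12-week outcome data. It does not say which variance is used, and the expectation rests mainly on the SD.

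**Conclusion.** The power statement is wrong as written for the declared primary outcome. On the plan's own inputs, 887 participants give about 73% power at week 12 from completers, and at most about 75% with recovery from earlier visits. Even with no missing data, power stays below 90%. The 90% figure is correct for the effect averaged over 2, 6 and 12 weeks, and carries over to a week-12 difference of 0.05 only if the effect is 0.05 at every visit.

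The size of the shortfall rests on SD 0.30, covariate correlation 0.5, 20% missing data and separate estimation of the week-12 effect. It does not follow that the trial is bound to be underpowered, because a true SD of about 0.237 or less would close the gap.

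**What to change.** In the Sample size section:

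- State that 887 was sized for the effect averaged over 2, 6 and 12 weeks.
- Give the power for the week-12 primary: about 73–75% for a difference of 0.05, or 90% for about 0.063, on the stated inputs.
- Specify that the re-estimation uses the variance of the week-12 contrast, so that N is not reduced on the averaged-score variance while week 12 remains primary.

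The cost is rewording one paragraph and the re-estimation specification, and a less favourable power figure. Correcting the statement needs no additional participants. Whether to recruit more can wait for the re-estimation, provided that it targets week 12.

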### Data analysis plan

The primary data analysis will be by intention to treat. A 5% two-sided significance level will be used throughout. A detailed statistical analysis plan will be developed by the study statisticians and finalised prior to locking of the trial database.

Analysis of the primary outcome will be a repeated measures analysis of covariance, including terms for treatment arm and the EQ-5D-5L responses at 2, 6 and 12 weeks. Adjustments will be made for the variables included in the randomisation minimisation algorithm. Adjustment for study site will be included as a random effect, if appropriate. The repeated measures approach enables estimation of an intervention effect at week 12 postrandomisation (primary outcome), and an overall assessment of the effect of the intervention over the 12-week period.

The 12-week NDI and Visual Analogue Scale will be analysed in a similar manner to the EQ-5D-5L. It is anticipated that results will underpin any between group differences seen in EQ-5D-5L, confirming and strengthening the clinical interpretation of the findings. All other secondary outcomes will be analysed with statistical models appropriate to the distribution of the outcome (see table 3). Where there are data recorded on multiple occasions postrandomisation, we may use an appropriate repeated measures model. Exploratory subgroup analyses by fracture type (I, II and III),^24^ CFS (<5 vs ≥5)^23^ and age (<75 vs ≥75 years) will be performed. The influence of any missing data on the robustness of the findings will be examined, for example, using multiple imputation models under a missing at random assumption. Screening logs will be analysed to assess generalisability of results.

**Table 3 T3:** Possible methods of analysis

Variable	Hypothesis	Outcome measures	Analysis methods
Baseline data	No difference between groups	Gender, age, comorbidities, injury data, radiological findings, inpatient management, CFS	Categorical variables: absolute numbers and percentages. Continuous variables: mean, median, SD, IQR.
Primary outcome			
Health-related quality of life at 12 weeks	Clinically important difference between two groups with early collar removal superior	EQ-5D-5L (continuous)	Repeated measures analysis of covariance at 2, 6 and 12 weeks, adjusting for minimisation variables
Secondary outcomes			
Pain	No difference between groups	NPRS (ordinal)	Ordinal regression
Function	No difference between groups	EQ-VAS (continuous), NDI (continuous) Grip strength (continuous) Bio impedance (ordinal)	Repeated measures analysis of covariance at 2, 6 and 12 weeks, adjusting for minimisation variables Student t-test Nonparametric methods; Mann-Whitney, Wilcoxon signed ranks test
Mortality	No difference between groups	All-cause mortality (binary)	Logistic regression, Χ^2^
Collar use	Significantly greater in the collar group	No of days of collar use (continuous)	Poisson regression
Health economics	Baysian assessment of likelihood incremental cost per QALY of either arm is below NICE Thresholds (£20 k to £30 k per QALY)	Service use & cost, QALYs (adjusted from EQ-5D-5L) Incremental Cost Per QALY	Generalised linear lodelling of cost and QALYs. Probabilistic sensitivity analysis via recycled predictions
Sub-group analysis;			
Fracture type (I, II and II)	No difference		For each analysis, the subgroup variable and interaction term between intervention and subgroup variable will be included in the model.
CFS (<5 vs ≥5)	Better treatment effect in CFS ≥5		
Age (<75 vs ≥75 years)	Better treatment effect in age ≥75		

Methods to be used for analysing variables collected in the DENS study. A detailed statistical analysis plan will be published.

CFS, Clinical Frailty Scale; DENS, Duration of External Neck Stabilisation; NDI, neck disability index; NICE, National Institute for Health and Care Excellence; NPRS, Numeric Pain Rating Scale; QALY, quality-adjusted life year; VAS, Visual Analogue Scale.

Interview data will be analysed thematically using the method of constant comparison. To ensure rigour, several individuals will be involved in data analysis and coding. An interactive working group will be set up, comprising the qualitative research team, co-investigators, the trial manager, patient and public involvement (PPI) representatives, and at least one healthcare professional from each of the sites involved in the pilot phase. A ‘what, so what, now what’ approach^32^ will be used to translate qualitative findings and other experiences shared by group members into tangible recommendations.

A 12-month within trial health economic analysis will be undertaken based on National Institute for Health and Care Excellence (NICE) reference case recommendations to maximise UK policy relevance.^33^ This will include: adoption of a National Health Service (NHS) and Personal Social Services decision perspective; cost-utility approach for primary analysis (results presented in terms of incremental cost per quality-adjusted life year (QALY), derived from EQ-5D-5L data with an area under the curve approach, omitting baseline); discount rate of 3.5% for both costs and QALYs (where applicable); and use of probabilistic sensitivity analysis, to generate cost-effectiveness acceptability curves via the recycled predictions technique.^33 34^ Choice of primary analysis cost per QALY threshold and EQ-5D-5L scoring algorithm will match NICE preferences at the time of data lock. Resource use will be combined with standard UK price weights to generate costs.^35 36^ The latest financial year for which at least one study participant provides data and prices are available will be selected as base year. Univariate mean QALYs, resource use and costs will be presented for each trial arm alongside differences in means and associated 95% CIs. Multivariate analysis of both QALYs and total costs, will also be presented controlling for baseline costs where available and minimisation variables. Missing data will be imputed using appropriate techniques depending on degree of missingness, likely multiple imputation by chained equations.

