### Randomisation and interventions

Web-based randomisation will occur with a minimisation algorithm based on:

Age at randomisation (<75 vs ≥75 years).Odontoid fracture type (I–III).^24^Frailty (CFS ≥5 vs <5).^23^

The first participant will be allocated to one arm with a probability of 0.5 and subsequent participants will be allocated with a probability of 0.8 to the group which minimises differences of the above variables between the two trial arms. Treatment allocation will be disclosed to the local research team via the web interface following randomisation.

The standard care arm will involve 12 weeks of hard collar treatment, following local usual choice of hard collar and local usual arrangements for collar care. For those allocated to the intervention (collar removal) arm, the collar will be removed as soon as possible, but may be weaned over several days if required for optimising analgesia. Removal of a collar prior to 12 weeks in the hard collar arm or wearing of a collar in the no collar arm will be recorded as a failure of adherence with explanation. Soft collars will not be used in either arm.

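### The protocol ties the primary adjustment to age and frailty as cut for minimisation, but does not say whether the 0.5 correlation behind the 25% sample-size saving refers to that form

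*Protocol article*

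**What the plan says.** Under Randomisation and interventions, the minimisation factors are "Age at randomisation (<75 vs ≥75 years"), odontoid fracture type I to III, and "Frailty (CFS ≥5 vs <5"). The article defines these factors nowhere else.

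Under Data analysis plan, the primary repeated measures analysis of covariance is specified as follows: "Adjustments will be made for the variables included in the randomisation minimisation algorithm". Table 3 repeats this by reference to the minimisation variables for the primary outcome and for EQ-VAS and NDI. Neither place states the coding of age or CFS in the model.

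Under Sample size, the target is reduced by "accounting for correlation between baseline covariates (age, CFS) and 12 week EQ-5D-5L". The size of the reduction is then given: "It is anticipated that this correlation will be around 0.5, allowing a 25% reduction in sample size". Again no coding is stated. Fracture type is not among the covariates credited.

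Table 1 shows EQ-5D-5L collected from 2 weeks onward and not at baseline. Age and CFS are therefore the only covariates credited with the 25% saving.

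**The concern.** The plain reading of the analysis section is that age and CFS enter as the algorithm uses them, each as a two-level factor. Cutting a graded covariate discards part of its association with the outcome. The Sample size section names age and CFS without cuts and leaves out fracture type, so it is not simply citing the minimisation set. The correlation of 0.5 could well have been meant for the uncut values.

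If so, the model as written would not deliver the variance reduction already built into 887. No baseline EQ-5D-5L is available to make up the difference. At stake is precision on the primary outcome. There is no question of bias, because adjusting for minimisation factors in cut form is valid.

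**Working it through.** **Inputs from the protocol (Sample size).** "An unadjusted sample size was calculated based on 90% power and a 5% significance level, using a two-sided two-sample t-test"; effect size from "0.05 minimum clinically important difference/0.3 SD"; "This results in a sample size of 1514, increasing to 1893 assuming 20% missing data"; covariate correlation 0.5; a further 37.5% reduction for repeated measures; final target 887, allocated 1:1. The 37.5% reduction is taken as given here.

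**Reproducing 887.**
- Per arm: 2 × (1.960 + 1.282)² / (1/6)² = 757 after rounding up, so 1514 in total.
- With 20% missing: 1514 / 0.8 = 1893.
- Covariate factor: 1 − 0.5² = 0.75. Repeated-measures factor: 1 − 0.375 = 0.625.
- 1893 × 0.75 × 0.625 = 887.3. The stated figure reproduces.

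**Power at 887 as planned.** Analysed per arm: 887 × 0.8 / 2 = 354.8. Residual SD: 0.3 × √(0.75 × 0.625) = 0.2054. Standard error: 0.2054 × √(2/354.8) = 0.01542. Then 0.05 / 0.01542 − 1.960 = 1.282, which gives 90.0%.

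**What the covariate saving is worth.** With none of it, N = 1893 × 0.625 = 1183, and power at 887 is about 80.2%.

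**Effect of cutting, one covariate score.** Assume a normally distributed score with R² = 0.25, cut so that a share p lies above the cut at standard normal quantile c. The fraction of R² kept is φ(c)² / [p(1 − p)]. Then N = 1183 × (1 − R²), and power follows as above.

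| Share above cut (assumed) | Fraction of R² kept | R² | N for 90% | Power at 887 |
|---|---|---|---|---|
| 50% | 0.637 (= 2/π) | 0.159 | 995 | 86.5% |
| 70% | 0.576 | 0.144 | 1013 | 85.9% |
| 80% | 0.490 | 0.122 | 1038 | 85.0% |

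For the median split, the saving is 15.9% instead of 25%, so 1 − 0.637 = 36% of it is lost.

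**Effect of cutting, two covariates.** Two correlated normal covariates, jointly giving R² = 0.25 uncut, were each cut and the outcome regressed on the two binaries (400,000 draws per scenario). All inputs here are assumptions, since the protocol gives no age or CFS distribution:
- correlation between age and CFS: 0, 0.3 or 0.5;
- relative correlations of age and CFS with the outcome: 0.2 and 0.45, 0.35 and 0.35, or 0.05 and 0.5, rescaled to the joint R²;
- shares above the two cuts (age, CFS): 50% and 50%, 70% and 50%, 80% and 40%, or 80% and 70%.

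Over the 36 combinations, R² is 0.124 to 0.178. The share of the saving lost is 29% to 50%, N for 90% power is 972 to 1036, and power at 887 is 85.1% to 87.2%.

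**If the 0.5 is already for the cut variables.** Nothing is lost and N stays 887. By the same median-split model, the uncut values would then carry an R² of about 0.25 / 0.637 = 0.39, so uncut adjustment would still be expected to gain precision.

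**The case against.** A reader might infer that the model definitely uses the cut versions, that the 0.5 definitely refers to uncut values, and that a fixed share of the saving, say a third, is therefore lost. The documents support none of these as fact.

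- **Form in the model.** The analysis section writes out the cuts for the subgroup analyses but not for the primary adjustment. The minimisation variables could be read as age and CFS themselves. Table 3 lists possible methods, and a detailed SAP, not shown, may settle the coding.
- **Form behind the 0.5.** The Sample size section does not say. If it is the modelled form, 887 is unaffected.
- **Size of the loss.** It depends entirely on assumed distributions and correlations.
- **Omissions in the check.** The two-binary calculation leaves out fracture type, which might recover a little precision.
- **Safeguards.** A sample size re-estimation on 12-week data from the first 300 participants is planned, and the protocol calls the assumed SD conservative. At R² = 0.16, a true SD of 0.30 × √(0.75/0.84) = 0.283 would offset the loss.

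These objections stand against any unconditional statement of a loss. They do not remove the point. The protocol fixes the covariate set by reference to factors that it defines only in cut form, so an SAP that follows it literally takes the cuts. The re-estimation could detect a shortfall if it uses the analysis model, but could make it up only by enrolling more participants. Uncut adjustment is expected to be at least as precise under either reading of the 0.5.

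**Conclusion.** The point holds conditionally. The adjustment and the sample-size saving are not aligned on the form of age and CFS. If the model uses the cuts and the 0.5 is for uncut values, roughly 30 to 50% of the 25% saving would be lost and power at 887 would be about 85 to 87% instead of 90%. That is a modest shortfall of about 3 to 5 percentage points.

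The range rests on near-normal covariates, the assumed splits and correlations, and the protocol's own SD, missing-data rate and repeated-measures factor. If the 0.5 refers to the cut variables, or if age and CFS enter uncut, the target of 887 stands on this point. The mismatch in the text is clear; the size of any loss is not something the documents can settle.

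**What to change.** In the Data analysis plan and the SAP, state that age in years and CFS grade enter the primary model as continuous or spline terms, together with fracture type. Do the same in the EQ-VAS and NDI models that share its form. Keep the cuts at 75 years and CFS 5 for minimisation and for the subgroup analyses. In the Sample size section, state that the 0.5 refers to age and CFS in that modelled form, and use the same model in the re-estimation on the first 300 participants.

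The cost is a sentence or two in each place. Age and CFS are already recorded at baseline, so no new data and no change to randomisation are needed. The change should be made before the SAP is finalised.
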